### Interventions

The study interventions are described in detail according to the Template for Intervention Description and Replication (TIDieR) guidelines (Hoffmann et al., 2014) in Table 1 to allow readers and other researchers to use or replicate the intervention.

**Table 1 T1:** **Description of study intervention based on the Template for Intervention Description and Replication (TIDieR) checklist (Hoffmann et al., 2014)**.

**Item**	**Experimental group**	**Control group**
1. Brief name	Fish oil + exergame training	Olive oil + exergame training
2. Why?	Exergame training (Bamidis et al., 2014) as well as omega-3 FA (Witte et al., 2014) have positive effects on the elderly brain. The combination of exergame training and omega-3 FA might improve brain structure and function more effectively than their sole administration.	Olive oil is not expected to induce better effects as omega-3 FA. Olive oil acts as a good comparator because of similarity in taste, composition, consistency, and color. Exergame training can improve brain structure and function, but on a lower level as compared to the experimental group.
3. What materials?	Participants receive bottles including the fish oil, measuring cups, and a NS diary to record adherence.	Participants receive bottles including the olive oil, measuring cups, and a NS diary to record adherence.
	On pressure sensitive dance plates, participants perform whole body movements driven by VGs presented on a frontal screen.	
4. What procedure?	The participants take the NS daily. The PE includes six different VGs whereas each VG adapts the difficulty level to the participant's abilities. Each exergame is designed to train different executive and physical functions. One 30 min-training includes one session of each VG (4 min) with short breaks (~1 min) for game change.	
5. Who provides?	Investigators instructed to NS and exergame training.	
6. How?	For the NS, both intervention groups receive initial instruction about intake, duration, and dosage by an exercised investigator. The PE is performed in small groups supervised by experienced investigators (master students in human movement sciences at ETH Zurich).	
7. Where?	The participants take the NS at home. The PE is performed in training rooms at ETH Hönggerberg (Switzerland).	
8. When and how much?	For 26 weeks, the participant takes 13.5 ml of the NS daily. After 16 weeks, the participants continue with the NS and start with the PE. The PE takes place three times per week (30 min) for 10 weeks.	
9. Tailoring	The PE is tailored to the abilities of each individual participant by the integrated progression algorithm. If a participant gets better/worse in performance, the VG automatically adapts and becomes more difficult/easier.	

*FA, fatty acid; NS, nutritional supplementation; PE, physical exercise; VG, video game*.

#### Nutritional supplementation

Participants randomized to the experimental group take a liquid (oily consistency) fish oil (San Omega AS, [name]). Participants randomized to the control group take olive oil as placebo (Oro del Desierto, [name]). The reasons for choosing olive oil as comparator are the similarity of taste, composition, consistency, and color. Thus, olive oil is the most commonly used placebo for omega-FA studies (Miller et al., 2014).

Over 26 weeks, the participants take a daily amount of 13.5 ml of fish oil, including 2.9 g of omega-3 FA, or 13.5 ml of olive oil. The first 16 weeks, the participants take the NS with the aim of reaching a steady state (Katan et al., 1997; Arterburn et al., 2006; Stonehouse, 2014). A review on omega-3 FA suggests that a duration of 16 weeks is needed to account for potential interaction effects of gender and age (Stonehouse, 2014). Moreover, the time frame of 16 weeks is the minimum time needed for red blood cells to reach a steady state (Katan et al., 1997; Arterburn et al., 2006). The duration and dosage of the omega-3 FA was based on findings of previous studies. Two studies showed no detectable cognitive benefits when considering an intake of 0.7 g for 24 months (Dangour et al., 2010) or 1.8 g for 26 weeks (van de Rest et al., 2014), respectively. A possible explanation might be that the dosage level is more important than the time frame. Witte et al. (2014) utilized 2.2 g for 26 weeks and achieved a significant increase of EF and beneficial effects in white-matter microstructure integrity and on gray-matter volume (Witte et al., 2014). A review identified low to moderate side effects in form of gastrointestinal upset, fishy aftertaste, worsening glycemia, and rise in low density lipoprotein cholesterol for 1–3 g/d of omega-3 FA (Kris-Etherton et al., 2003).

At home, the NS can be taken undiluted or can be added to food (e.g., salads) or drinks. At intervention start, the participants receive bottles including the NS, measuring cups (13.5 ml), and oral as well as written information about duration, dosage, and intake. To check for intake adherence, the participants are supplied with a NS diary including week days and daytime.

#### Exergame training

On a pressure-sensitive dance plate (Impact Dance Platform, 87.5 × 87.5 × 2.5 cm, Positive Gaming BV, BZ Haarlem, Nederland), the participants perform specific whole body movements triggered by a video game (VG) presented on a frontal screen. The dance pad is connected by USB to a desktop computer and with symbols projected on a wall using a beamer. Electronic sensors in the dance pad detect position and timing information that are used to provide participants with real-time visual and auditory feedback. Through foot pushes on the plate arrows (right, left, top, and bottom), the participants interact with the game. The VGs (dividat, Schindellegi, Switzerland) are designed to train different aspects of EFs (divided attention, working memory, inhibition, and shifting) and physical functions. The exergame training allows the implementation of training principles as described in the paper of Healy et al. (2014) a feedback system to facilitate training, individual levels of difficulty according to individual skills and abilities, adjustable task difficulty to facilitate retention, and variability of training to enhance task transfer. Additionally, the FITT training principles are implemented; Frequency: three times per week, Intensity: individually adapted VG (allowing training progression), Type: combination of cognitive and motor training, and Time: 30 min training sessions.

After 16 weeks of NS intake, all participants start to perform the exergame training that lasts 10 weeks. The participants train for 30 min, three times per week. Based on the results of a meta-analysis, the time frame of 10 weeks was chosen in terms of an expected effect size of 0.478 (Colcombe and Kramer, 2003). The time frame and training intensity were, furthermore, based upon studies illustrating positive training effects in older adults performing a VG on a dance plate (Pichierri et al., 2012a,b). Training includes one session of each VG (4 min) in a pre-defined order and short breaks (~1 min) for game change. In training rooms (ETH Hönggerberg, Switzerland), the participants perform their exercises in small groups supervised by experienced investigators. To control for adherence, the participants receive a training plan including dates and time schedule. Furthermore, the investigators control adherence by a training adherence checklist. A previous trial testing the effects of similar games in older adults showed that this program will effect on EFs (Schättin et al., 2016).

### Staff eligibility

All involved investigators received training for data collection and handling in accordance with the study measurement protocols. Additionally, the investigators were instructed on how to prepare the participants for correct maintenance of the diary and NS intake. Furthermore, the investigators guiding the PE got instructions about the handling of the game console, game software, and the training procedure. The trained investigators supervise PE to explain the VG (if needed) and to minimize the risk of falls.

### Outcomes

All measurements are performed at pre- and post-intervention. The primary and secondary outcomes are listed in Table 2.

**Table 2 T2:** **Trial outcomes**.

**Assessment methodology**	**Outcomes**	**Indication**
**PRIMARY OUTCOME**		
TMS	Motor evoked potential (right M. tibialis anterior)	Excitability of neuronal system, indirect measure of synaptic plasticity (Voss et al., 2013)
EEG	Response-related potential	Neuronal activity
**SECONDARY OUTCOME**		
TAP	Reaction time	Cognitive functioning
Gait	Temporal and spatial parameters	Motor functioning
	DTC	Cognitive cost
Blood sample	FA levels	Indicator for NS
**OTHER OUTCOMES**		
Short FES-I	Points (7–28)	“Concern” about falling
MMSE	Points (0–30)	Mental status
GDS	Points (0–15)	Depression status

*DTC, dual-task cost; EEG, electroencephalography; FES-I, falls efficacy scale international; GDS, geriatric depression scale; MMSE, mini mental state examination; NS, nutritional supplementation; TAP, test for attentional performance; TMS, transcranial magnetic stimulation*.

#### Transcranial magnetic stimulation

Participants sit comfortably on an adjustable chair with hip, knee, and ankle joint angles of 100°, 120°, and 90°, respectively. Given the symmetrical nature of transcranial magnetic stimulation (TMS)-related measurements of the lower limb, only the dominant side is assessed (Cacchio et al., 2009). Cortical stimulation is applied by means of a TMS stimulator MAGSTIM 200 (Magstim Company Ltd., Whitland, Dyfed, UK) with a “figure of eight” coil placed over the cortical motor area to stimulate the right M. tibialis anterior (TA). In healthy participants, TMS-related measurements of the TA are reliable (Cacchio et al., 2009).

Muscle activity is recorded by Telemyo DTS (Noraxon, Cologne, Germany). Before the measurement, the skin of the shank is shaved (if needed) and prepared with an abrasive gel (OneStep AbrasivPlus, H+H Medizinprodukte, Münster, Germany). The electrodes (Ambu® Blue Sensor N, Cambridgeshire, UK) are placed with an inter-distance of two cm on the muscle belly of the right TA. The muscle belly is defined through contraction of the TA.

In the first step, the participants are handed a bathing cap that fits tightly on the head. On the top of the cap, a grid is drawn using the vertex as initial position. The vertex is determined as half distance from nasion to inion and half distance from right to left pre-tragus. As previously suggested, the optimal activation of the TA is obtained if the coil is placed parallel to and approximately 0.5–1.0 cm lateral to the midline and its mid-point is aligned anterior-posteriorly against the vertex (Cz) (Devanne et al., 1997). To maintain consistent coil positioning across sessions, detailed distance recordings are made from the nasion, inion, and bilateral pre-tragus to the vertex. In the second step, the optimal stimulation point is assessed (hotspot). The hotspot corresponds, on the grid, to the lowest motor threshold that evokes a motor evoked potential (MEP) response (Rossini et al., 1994). The third step involves determination of the resting motor threshold (RMT) defined as the lowest intensity of magnetic stimulation required to evoke MEPs of 50 μV in peak-to-peak amplitude in at least 6 of 10 consecutive trials (Rossini et al., 1994). In the fourth step, a recruitment curve (RC) of increasing intensities of 10% steps is obtained in 10 trials per step. The stimuli intensities from 90% RMT to 140% RMT are applied in a random order. The interval between the stimuli is 7 s with a 20% variance to avoid familiarization. The analysis of peak-to-peak amplitude (MEP) and RC will be performed in Matlab™ for Windows (Mathworks Inc., Natick, MA, USA).

#### Electroencephalography

For electroencephalography (EEG) measurement, the participants wear a 20-channel dry-electrodes Enobio device (Neuroelectrics, Barcelona, Spain; Ruffini et al., 2006, 2007). The EEG system records and visualizes 24 bit EEG data at 500 Hz. The device sends the data via wireless connections to a personal computer where data can be monitored in real-time. During the EEG recording, the participants perform a Go/No-Go task including the suppression of a response in the presence of irrelevant stimuli. The stimuli presentation of the Go/No-Go task stems from the Test for Attentional Performance (TAP). The task is presented on a personal computer screen in front of the participants for about 10 min (five times 2 min). On a keyboard, the participants have to push a predefined button when the relevant stimuli appear. One investigator records the right and wrong event-related responses of the participants comparing the stimuli of the Go/No-Go task and the trigger appearing on the EEG screen. At the time point of clicking, a trigger is recorded and integrated into the EEG data recording. The trigger time points will be used for further analysis of the EEG data including response-related potentials (RRP). The analysis will be performed in Matlab™ for Windows (Mathworks Inc., Natick, MA, USA).

#### Test for attentional performance

The TAP (D-TAP 2.3 VL, PSYTEST, Psychologische Testsysteme, Herzogenrath, Germany) was initially developed to assess deficits in attention. The TAP is a valid test with the subtests measuring different and statistically independent attentional aspects (Zimmermann and Fimm, 2002). On a frontal screen, the participants see each test running on a personal computer. A button, placed in front of the participants, is used to record the reaction time and failure rate of the participants. Before the main test starts, the participants perform a pre-test to clarify the procedure and to minimize possible learning effects. The participants execute two tests: (1) Working memory (5 min): The participant has to compare presented double-digit numbers on the screen with previously exposed double-digit numbers. By pressing the button, the participants indicate the repetition of a number within a short interval; and (2) Divided attention (3.25 min): This subtest consists of visual and acoustic signals presented in an asynchronous way. In a 4 × 4 matrix, the visual task consisting of crosses appearing in a random configuration. The acoustic part consists of low and high beeps playing in a regular sequence. The participant has to detect whether the cross forms the corners of a square or whether the beeps have an irregularity in their sequence.

#### Gait analysis

Temporal (time) and spatial (distance) gait parameters are measured with the Physilog (Gait up Sàrl, Lausanne, Switzerland) via wearable standalone movement sensors (50 × 37 × 9.2 mm, 19 g, anatomical curved shape) containing inertial sensors. A button on the sensors allows the start and stop of measurement. A micro-USB port allows data transfer to the personal computer for further analysis of gait performance data. Physilog provides objective, quantitative, and valid assessment of gait movement (Aminian et al., 1999; Dubost et al., 2006; de Bruin et al., 2007; Mariani et al., 2012). The sensors are fixed with elastic straps at the right and left forefoot of the participants for flat over ground gait analysis over a distance of 10 m. Participants perform a single-task condition (preferred walking) and a dual-task condition, i.e., preferred walking whilst counting backwards in sevens from a random given number. The participants are instructed to position themselves at the beginning of the walkway and are asked to walk with their comfortable speed to the end of the walkway. Thereafter, the participants are asked to perform the same walking task while counting. For counting, the participants get a random number between 200 and 250 at the start. The instructions are standardized as follows: (1) “Walk with your comfortable speed right to the end of the walkway.” (2) “Walk with your comfortable speed right to the end of the walkway counting backwards from [random number between 200 and 250].” The participants have to count loud and don't stop walking; otherwise, the trial is recorded as failure. Instructions are given that no one task should be prioritized over the other. Assistive devices like canes, crutches or walking frames can be used if necessary. Each tested condition is repeated three successful times to obtain representative samples and the means of the three successful trials will be used for further data analysis. For each participant the relative dual-task costs (DTC) of walking, as percentage of loss relative to the single-task walking performance, according to the formula DTC [%] = 100^*^ (single-task score-dual-task score)/ single-task score (McDowd, 1986) will be calculated.

#### Blood sample

Venous blood samples are collected by a qualified investigator and stored in 2.7 ml EDTA tubes (S-Monovette, K3 EDTA, 75 × 13 mm, Sarstedt, Germany). Blood samples are taken to analyze FA values in erythrocytes. This direct method for FA analysis is reliable and accurate with Limits of Detection of the FAs profiles ranging between 0.23 and 3.19 μg (Rodriguez-Palmero et al., 1998). Pre- and post-dosage FA values will be assessed and compared with reference values previously reported (Superko et al., 2013). The FA parameters will be analyzed by Omegametrix GmbH (Martinsired, Germany). The laboratory meets the strict criteria of the quality standard DIN ISO 15189.

#### Mini mental state examination

The Mini Mental State Examination (MMSE) is a reliable and valid test to quantitatively estimate the severity of cognitive impairment (Folstein et al., 1975; Tombaugh and McIntyre, 1992). The 30 questions of the MMSE are categorized into seven categories: (1) orientation to time, (2) orientation to place, (3) registration of three words, (4) attention and calculation, (5) recall of three words, (6) language, and (7) visual construction. An investigator performs the test with the participants by giving zero points or one point for incorrect or correct answer, respectively.

#### Geriatric depression scale

The Geriatric Depression Scale (GDS) is a self-report questionnaire to identify depression in older adults (Yesavage et al., 1983). The GDS is a valid and reliable depression screening (Yesavage et al., 1983). The short form has 15 questions focusing on worries of the participants, and the way they conceive and interpret their quality of life (Yesavage and Sheikh, 1986). The questionnaire can be answered in a yes/no response.

### Data collection

All consenting participants received a case report form (CRF) to ensure that eligibility criteria are met and to ensure all measurements are performed. The CRF includes a confirmation that participants read the information sheet and signed the informed consent. Furthermore, the list of inclusion and exclusion criteria is included to confirm the eligibility of the participants. For the measurements, the steps are cross-checked for digital recording data (TMS, EEG, TAP, and gait), results are noted (short FES-I, GDS, MMSE) and blood taking is confirmed. The data from TMS, EEG, TAP, and gait are stored on a personal computer for further analysis. Any digital data, blood samples, questionnaires, and CRFs are coded with the individuals' ID.

### Sample size

To avoid a type I or II error, the power calculation was based on a study examining the effect of omega-3 FA on EEG frequency band distribution during a sustained attention test (Fontani et al., 2005). The aforementioned study was used for sample size calculation because so far there exists no study that examined the influence of exergame training in combination with omega-3 FA on neuronal systems using TMS or EEG methodology. Due to the values of EEG frequency band distribution during sustained attention tests (with values K + K = 27.70 ± 5.2; K + K = 31.49 ± 8.6), an estimated sample size of 24 participants would result in 80% power at an alpha-level of 0.05 for this parameter. To account and compensate for expected drop-outs, the study includes 30 participants in each group. Drop-outs are expected because of the long study duration of 26 weeks, the age of the participants, and numbers are based on previous reports on adherence of non-institutionalized older adults to exercise programs (Nyman and Victor, 2012).

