## Abstract

A common problem in the older population is the risk of falling and related injury, immobility, and reduced survival. Age-related neuronal changes, e.g., decline in gray-and white-matter, affect neuronal, cognitive, and motor functioning. The improvement of these factors might decrease fall events in elderly. Studies showed that administration of video game-based physical exercise, a so-called exergame, or omega-3 fatty acid (FA) may improve motor and/or cognitive functioning through neuronal changes in the brain of older adults. The aim of this study is to assess the effects of a combination of exergame training with omega-3 FA supplementation on the elderly brain. We hypothesize that an intervention using a combination approach differently affects on the neuronal structure and function of the elderly's brain as compared to the sole administration of exergame training. The study is a parallel, double-blinded, randomized controlled trial lasting 26 weeks. Sixty autonomous living, non-smoking, and right-handed healthy older (>65 years) adults who live independently or in a senior residency are included, randomized, and allocated to one of two study groups. The experimental group receives a daily amount of 13.5 ml fish oil (including 2.9 g of omega-3 FA), whereas the control group receives a daily amount of 13.5 ml olive oil for 26 weeks. After 16 weeks, both groups start with an exergame training program three times per week. Measurements are performed on three time-points by treatment blinded investigators: pre-intervention measurements, blood sample after 16 week, and post-intervention measurements. The main outcomes are motor evoked potentials of the right M. tibialis anterior (transcranial magnetic stimulation) and response-related potentials (electroencephalography) during a cognitive test. For secondary outcomes, reaction time during cognitive tests and spatio-temporal parameters during gait performance are measured. Statistics will include effect sizes and a 2 × 2-ANOVA with normally distributed data or the non-parametric equivalent for data not fulfilling normal distribution. The randomized controlled study is the first to investigate the effectiveness of exergame training combined with omega-3 FA in counteracting age- and behavioral-dependent neuronal changes in the brain. This study has been registered in the Swiss National Clinical Trials (SNCTP000001623) and the ISRCTN (ISRCTN12084831) Portals.

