A systematic review revealed that previous interventions using a combined approach of PE and NS to effect on the brain were not particularly successful because of the misfit between the combinations; the intervention components were not selected based on sharing of similar neuronal mechanisms (Schättin et al., 2016). The review indicates, however, that especially fish oil, containing omega-3 fatty acid (FA), might be an effective NS supporting the positive effects of PE. Omega-3 FA is important for energy metabolism and for the composition of the plasma membranes in the brain (Gómez-Pinilla, 2008). Another review showed that long chain polyunsaturated FA (LCPUFA) might improve cognition, decrease (neuro) inflammation, and reduce vascular risk factors in normal aging adults (Janssen and Kiliaan, 2014). Omega-3 LCPUFA may provide decreased brain deterioration through the positive effects on brain structure, function, and cerebral blood flow (Haast and Kiliaan, 2015). A recent randomized-controlled study showed that fish oil had positive effects on brain structure and function in healthy older adults (Witte et al., 2014). The participants showed improved EFs, white matter microstructure integrity, gray matter volume, and vascular parameters.

So far no study investigated the combined effect of exergame training and omega-3 FA on the elderly brain's structure and function. This study, therefore, aims to investigate the effects of a combination of exergame training and omega-3 FA. The following research question will guide through the research process: “Does the combination of exergame training and fish oil differently affect neuronal system levels in the elderly brain compared to exergame training alone?” The main objectives of the trial are (1) to determine the effects of the intervention on the neuronal structural level of the brain (neuronal excitability) and (2) to assess the effects on functional level in the brain (neuronal activity). We hypothesize that the combination will differently affect these parameters.

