### Blinding, randomization, and allocation

The NS, packed in bottles equal in outer appearance, were blinded by an external center (Kantonsapotheke Zurich, Switzerland) to achieve double blinding. The external center created a computer-generated list including numbers from 001 to 060 that correspond to either fish oil or olive oil, respectively. The list number does not correspond to the participants' identification (ID) number. The list consists of six blocks of ten whereas fish oil and olive oil are randomly and equally distributed in all blocks. The investigators continuously assigned the volunteering women to the numbers starting with 001 and ending with 030 and the men starting with 031 and ending with 060. The randomization list is stored by a non-involved investigator and out of reach and sight of the involved investigators. For statistics, the groups will be referred to without specification of NS (e.g., group A and B).

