### Statistics

The data analysis will be performed at the end of intervention including the measurement values from pre- and post-intervention measurements. Data will be tested for normal distribution using Shapiro-Wilk test and Q-Q-plots. A 2 × 2-ANOVA will be used with normally distributed data, the non-parametric equivalent for data not fulfilling assumptions of normal distribution. The test will be used to compare the two interventions over time (from pre- to post-measurement) on changes on the main dependent variables MEP, RRP, RT of cognitive tasks, spatio-temporal gait parameters, DTC, and FA levels. In addition to statistical significance testing effect size calculation (*r* = Z/√N) will be performed. The participants' FA blood levels, demographic, and health information will be examined in relation to the outcome measures in order to interpret the results in context. All statistical procedures will be conducted with the IBM Statistical Package for the Social Science software package. A probability level of *p* < 0.05 will be considered to be statistically significant.

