## Anticipated results

The results of this study can be influenced by several factors. One might be the adherence to regular intake of the NS. As countermeasures an intake protocol supports the participant and helps the investigator to control the intake. Blood sample analysis is an additional control measure. Moreover, the training attendance is checked by the investigators, so that each participant reaches at least 70% attendance. However, a higher drop-out rate may be expected because of the long trial duration. The aforementioned sample size calculation included the calculated 25 participants and five additional participants for each intervention group because of the expected drop-outs. Moreover, TMS is used in this study as an indirect proxy measure of synaptic plasticity. Based on the results of this study future studies should focus on more direct measures of synaptic plasticity by using either magnetic resonance tomography (Alvarez-Salvado et al., 2014) or positron emissions tomography scans (Magistretti, 2006) for comparing the brain scans before and after the intervention.

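### The values quoted for the sample size do not support 80% power with 24 or 25 per arm unless an unstated assumption is made, such as a pre-post correlation of about 0.79

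*Protocol article*

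**What the plan says.** The Sample size section takes its inputs from an earlier study of omega-3 and EEG frequency bands during a sustained attention test ("with values K + K = 27.70 ± 5.2; K + K = 31.49 ± 8.6") and concludes that "an estimated sample size of 24 participants would result in 80% power at an alpha-level of 0.05 for this parameter". It then allows for drop-out: "the study includes 30 participants in each group". The sentence with 24 does not say whether this is a total or a per-group number. Anticipated results settles that it is per group but gives a different figure: "the calculated 25 participants and five additional participants for each intervention group because of the expected drop-outs".

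The rest of the article fixes the design to which the calculation must apply:
- Abstract: "The study is a parallel, double-blinded, randomized controlled trial lasting 26 weeks".
- Blinding, randomization, and allocation: "fish oil and olive oil are randomly and equally distributed in all blocks", so allocation is 1:1.
- Introduction: "We hypothesize that the combination will differently affect these parameters", which is non-directional.
- Statistics, on the 2 × 2 ANOVA: "The test will be used to compare the two interventions over time (from pre- to post-measurement").

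For the calculation itself the article states no test, sidedness, correlation or SD of change. It does not say whether the two quoted values are two groups or two occasions, or whether ± is an SD.

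**The concern.** The article prints both the inputs and the result of its power calculation, so a reader can check it, and the obvious check fails. For two independent arms and a two-sided 5% test, the quoted means and SDs call for more than twice the stated number per arm. This calculation is the only justification given for the size of the trial. If 80% is taken at face value but the real figure is nearer one half, a true effect of the assumed size would be missed about as often as found. A non-significant result would then look more informative about the added value of fish oil than it is.

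**Working it through.** **Inputs** (Sample size section, ± read as SD): means 27.70 and 31.49; SDs 5.2 and 8.6; α = 0.05; stated n = 24 (25 in Anticipated results), enrolled 30 per arm. Two-sided testing is assumed because the hypothesis is non-directional.

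**Effect size**
- Difference D = 31.49 − 27.70 = 3.79
- Pooled SD = √[(5.2² + 8.6²)/2] = √[(27.04 + 73.96)/2] = √50.5 = 7.106
- d = 3.79/7.106 = 0.533

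**Step 1. Trying to reproduce 24 from the quoted means and SDs.** Two-arm readings, n per arm for 80% power (noncentral t):

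| Reading | n per arm | Power at 24 per arm |
|---|---|---|
| Two-sided, pooled SD 7.106 | 57 | 44% |
| One-sided, pooled SD 7.106 | 45 | 57% |
| Two-sided, SD 5.2 only | 31 | 70% |
| One-sided, SD 5.2 only | 24 | 80% |
| Two-sided, SD 8.6 only | 82 | 32% |

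The normal approximation for the first row is 2(1.96 + 0.842)²/0.533², which rounds up to 56. A Welch test, allowing unequal SDs, also needs 57. Only the one-sided calculation that drops the SD of 8.6 returns 24.

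Within-person readings use SD of difference = √(101.0 − 89.44 r). Two-sided, 24 people suffice at r ≈ 0.68 (33 are needed at r = 0.5). One-sided, 24 suffice at r ≈ 0.565, where the SD of the difference is about 7.1. These are contrasts within one group, not between arms.

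**Step 2. Two-sided between-arm power at the article's numbers.** Noncentrality = d√(n/2), with 2n − 2 degrees of freedom:
- 24 per arm: 44.0%
- 25 per arm: 45.5% (46% rounded from 45.54%)
- 30 per arm, no drop-out: 52.8%
- 24 in total (12 per arm): 23.9%

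**Step 3. The planned group-by-time contrast.** With two visits, the interaction in the 2 × 2 ANOVA equals a two-sample test on change. Assume that 3.79 is the between-arm difference in change and 7.106 the SD at each visit. With pre-post correlation r, the SD of change is 7.106√[2(1 − r)] and the effect size is 0.533/√[2(1 − r)].

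| r | SD of change | Effect size | Power, 24 per arm | Power, 30 per arm |
|---|---|---|---|---|
| 0.3 | 8.41 | 0.451 | 33% | 40% |
| 0.5 | 7.11 | 0.533 | 44% | 53% |
| 0.7 | 5.50 | 0.689 | 65% | 75% |
| 0.8 | 4.49 | 0.843 | 82% | 89% |

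**Step 4. Detectable effect and the correlation needed.** The effect detectable with 80% power, standardised by the SD of whatever is analysed, is 0.826 at 24 per arm and 0.736 at 30. Setting 0.533/√[2(1 − r)] equal to these gives r = 1 − 0.533²/(2 × 0.826²) ≈ 0.79 at 24 per arm, and r = 1 − 0.533²/(2 × 0.736²) ≈ 0.74 at 30.

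**The case against.** The strongest reply is that the trial will not compare single values. The Statistics section plans a pre/post comparison between arms, and there 24 per arm does reach 80% if the correlation is about 0.79. This stands. A reader might infer that 24 arises only from calculations that do not fit the trial, or that 44% is the power of this design. The documents support neither: 44% belongs to a single-value comparison, or to change at a correlation of exactly 0.5. What does not follow is that 80% is thereby justified, because the article states no correlation and one near 0.8 is demanding.

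A repeated-measures routine that takes f = d/2 = 0.267 as the interaction effect is more generous: about 80% with 24 in total at r = 0.6, and 95% with 48 in total at r = 0.5. But an interaction f of 0.267 means a difference in change of 4 × 0.267 × 7.106 ≈ 7.58, which is twice the quoted 3.79.

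It can also be said that the source calculation may be sound for some other contrast. Both values carry the same label, which may be symbols lost in text conversion, and the cited study is not at hand. So an arithmetic slip is not shown; a calculation that does not match the two-arm design is at least as likely. If ± denotes standard errors, the shortfall is larger.

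Finally, the claim is confined to a borrowed EEG frequency-band value, not to the motor evoked or response-related potentials, and the article nowhere says that a null result will be read as no added effect. Both are fair limits on the consequences, but neither makes the printed 80% follow from the printed inputs.

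**Conclusion.** The point holds in a conditional form. The quoted values do not support 80% power with either 24 or 25 per arm for a two-arm, two-sided comparison. On single values the need is 57 per arm, and power is 44%, 46% and 53% at 24, 25 and 30 per arm. On the planned group-by-time contrast, power at 24 per arm runs from 33% to 82% as the pre-post correlation goes from 0.3 to 0.8, and at 30 per arm from 40% to 89%.

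Every reading examined that returns the stated figure needs an assumption the article does not state (a high correlation, a one-sided test that drops one SD, or a doubled difference) or a contrast that is not between arms. The result rests on ± being an SD, on two-sided testing, and, for the planned contrast, on 3.79 as the difference in change with SD 7.1 at each visit. The stated power should be corrected or its missing assumption supplied, and 24 and 25 cannot both be the calculated number.

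**What to change.** Replace the 80% sentence with the power of the planned between-arm pre/post contrast, naming the test, the sidedness and the assumed pre-post correlation. Suitable wording: *For a between-arm difference in change of 3.79 with SD 7.1 at each visit (two-sided 5%), 24 evaluable participants per arm give 33%, 44%, 65% and 82% power at pre-post correlations of 0.3, 0.5, 0.7 and 0.8; 30 per arm give 40%, 53%, 75% and 89%. The effect detectable with 80% power, in SDs of the analysed quantity, is 0.83 with 24 and 0.74 with 30 per arm.*

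If a particular correlation or a paired contrast lay behind the 24, state it with its source. Say what the two quoted values are and whether ± is an SD. Make the Sample size and Anticipated results sections give the same calculated number per group.

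The cost is a few sentences and a less favourable stated power. No change of design and no extra enrolment is needed.
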